## Power and Sample Size

Statistical Power and sample size were determined using a simulation programed in SAS 9.3. The simulation generated data with a range of intra-class correlations (ICC) from .04 to .08, and an information control condition with a proportion of clients’ HIV testing of 20% as found in the control condition in CTN0032, a study assessing the relative effectiveness of three HIV testing strategies on increasing receipt of test results and reducing HIV risk behaviors among patients seen at drug use treatment centers.(32) A sample size of 51 OTPs and an average of about 100 clients per site per 6- month period provides over 95% power for the primary outcome and 80% power for the secondary outcome if the proportion of clients’ HIV testing in the HIV PC condition is 30% (absolute difference of 10% from control condition) and the proportion of clients’ HIV testing in the HIV/HCV PC condition is 41% (absolute difference of 11% from the HIV PC condition) for all expected levels of ICC (.04 to .08). For the quasi-experimental evaluation of the blending product, the study will have over 80% power to uncover an absolute change in proportion testing for HIV of 6% to 7%. For analysis of change in proportion of facilitators/barriers, the study will have over 80% power to uncover a significant difference in change if the difference in change is .5 to .65 of a standard deviation, a medium effect size.

## Empirical Analysis

The primary outcome analysis will test the hypothesis that the two PC interventions will result in significantly higher proportions of clients tested for HIV than the control condition during the “initial impact” period (7–12 months post-randomization or T3), controlling for the proportion of clients tested during the baseline period (T1). We will use a generalized estimating equation (GEE) model with a binary distribution and logit link. The model will include four 6-month periods: T1 (months -6 to-1) -- prior to randomization, T2 (months 1–6) -- during intervention/control period, T3 (months 7–12) -- initial impact, and T4 (months 13–18) -- sustained impact. Time and participants are both nested within site. However, time is not nested within participants in the primary analysis. Individuals within a site may be more alike (correlated) than are individuals between sites, which will be accounted for in the GEE by inclusion of the working correlation matrix within site and the sandwich estimator for standard errors. The model will include gender and race/ethnicity, and geographic region as control variables. The primary tests of H1 will be done using a contrast of testing differences across conditions in the proportion of clients tested during T3, controlling for the proportion of clients tested pre-randomization (T1).

The secondary and tertiary outcome analyses will use similar GEE methods as described for the primary outcome measure. The secondary outcome will test the hypothesis that the HIV/HCV PC intervention will result in significantly higher proportions of clients tested for HIV than the HIV PC intervention during the initial impact period (7–12 months post-randomization or T3), controlling for the proportion of clients tested during the baseline period (T1). Other secondary measures will examine, for example, the impact of the PC interventions on the provision and sustainability of HIV testing (T4), the impact of the PC interventions on initial impact of HCV testing (T3). The tertiary outcome analysis related to linkage to care will evaluate the effectiveness of the interventions relative to the control condition on linkage to HIV care among OTP clients who tested positive for HIV, or for HCV, as well as change in perceived barriers/facilitators to HIV testing.

We will use mixed-methods to evaluate the impact of the PC interventions and the OTPs’ organizational and environmental characteristics that serve as facilitators and barriers to the provision and uptake of HIV testing (T3), sustained implementation of HIV testing (T4), and improving timely linkage to care for persons who test positive. We will use a multilevel GEE model to examine whether change in perceived barrier/facilitators mediates intervention impact on HIV testing (T4). Mediation will be assessed by the product of coefficients method.

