## Methods/Design

### Study Design

This protocol manuscript follows the SPIRIT reporting guidelines (27). The design is a 3-arm cluster-RCT of sites treating opioid use disorder in the U.S. Fifty-one OTPs are randomly assigned to one of three conditions (17 sites per condition) – information only control arm, PC to initiate or increase HIV testing and linkage to care, and PC to initiate or increase HIV and HCV testing and linkage to care (Figure 1). The study tests the effect of two active evidence-based PC interventions against an informational control on the provision and sustained implementation of on-site HIV testing and linkage to care, and on-site HIV/HCV testing and linkage to care, among OTP clients.

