### Randomization

Sites are randomized into three groups (HIV PC, HIV/HCV PC, and information only control condition) in a ratio of 1:1:1 using a blocked randomization scheme to ensure relative balance across time of entry into the study. The data analyst, who is not involved in the delivery of the intervention, keeps the randomization schedule and sequence secure, and ensures confidentiality and independence of the allocation data. After site personnel complete baseline surveys and interviews, site personnel are notified to which of the three study conditions the site has been assigned.

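### Sandwich-based GEE inference with 17 sites per arm names no small-sample correction; without one, a nominal 5% test of the primary contrast would run at about 7–9%, or 8–11% under less favourable models

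*Protocol article*

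**What the plan says.** The Empirical Analysis section specifies a "generalized estimating equation (GEE) model with a binary distribution and logit link" covering four six-month periods, T1 to T4. The primary test is a contrast between conditions at T3, adjusted for T1. Within-site correlation is handled by "inclusion of the working correlation matrix within site and the sandwich estimator for standard errors". On covariates: "The model will include gender and race/ethnicity, and geographic region as control variables". Secondary and tertiary outcomes are to be analysed by similar GEE methods.

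The number of clusters is fixed in Study Design ("17 sites per condition", 51 in all) and in Randomization ("in a ratio of 1:1:1 using a blocked randomization scheme"). Power and Sample Size assumes "A sample size of 51 OTPs and an average of about 100 clients per site" per six-month period and "a range of intra-class correlations (ICC) from .04 to .08". It claims over 95% power for the primary outcome and 80% for the secondary one, with testing rates of 20%, 30% and 41%.

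The article gives no significance level or sidedness, no small-sample variance correction and no reference distribution.

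**The concern.** The sandwich variance is justified as the number of clusters grows. With few clusters the fitted model follows the data too closely: residuals are too small, so the estimated variance is too low. The estimate is also noisy, so a normal or chi-square reference has tails that are too thin. Both effects make the test anti-conservative. They worsen with more site-level terms (arms, region, T1 rate) and with unequal site sizes. Unequal sizes are to be expected here, because eligibility sets a minimum client volume and no maximum.

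At stake is the error rate of the primary claim and of every other contrast that uses the same method. Intervals would be too narrow, and an ineffective intervention would be declared effective more often than the nominal level allows.

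**Working it through.** **1. The plan's own power figures.** Each arm has 17 × 100 = 1,700 clients. The design effect is 1 + 99 × ICC, which is 4.96, 6.94 and 8.92 at ICC .04, .06 and .08. The effective size per arm is 342.7, 245.0 and 190.6. Power = Φ[(d − 1.96·SE0)/SE1], with SE0 from the pooled rate and SE1 from the separate rates.

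- Primary, 20% against the pooled PC rate (30 + 41)/2 = 35.5%. At ICC .08: (0.155 − 1.96 × 0.0408)/0.0380 ≈ 1.98, giving 97.6%. At .04 and .06 power is 100% and 99.4%. The stated figure of over 95% is reproduced.
- Secondary, 30% against 41%. At ICC .08: (0.11 − 1.96 × 0.0490)/0.0487 ≈ 0.29, giving 61.3%. At .04 and .06 it is 85.5% and 72.2%. The stated 80% at ICC .08 therefore needs a strong gain from baseline adjustment.

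**2. Type I error by simulation.**

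- From the article: 51 sites at 17:17:17, about 100 clients per site and period, a 20% rate, and ICC .06 (middle of its range).
- Assumed: two-sided 5%; logit-normal site effects; 0.8 of the site variance shared between periods; gender, four race/ethnicity levels and four regions; site-size coefficient of variation (CV) 0, 0.5 or 0.8.
- Two readings of the model: four periods with arm × period (12 cells + 1 gender + 3 race/ethnicity + 3 region = 19 parameters), or T3 with the site's T1 logit as a covariate (1 + 2 + 1 + 1 + 3 + 3 = 11 parameters).
- There were 3,004 replicates per scenario, with a Monte Carlo error of about 0.5 points. The t reference has 44–45 df.

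The table gives rejection rates (%) under no effect. KC is Kauermann-Carroll, MD is Mancl-DeRouen, and r is the robust SE divided by the empirical SD for the pooled contrast.

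| Model, site-size CV, working correlation | r | Plain z, pooled PC v control | Plain z, pairwise | Plain, 2-df | KC + t, pooled | MD + t, pooled |
|---|---|---|---|---|---|---|
| Four-period, 0 | .958 | 6.8 | 6.6–7.8 | 9.1 | 5.4 | 4.8 |
| Four-period, 0.5, exchangeable | .930 | 8.4 | 7.2–8.1 | 10.0 | 6.4 | 5.2 |
| Four-period, 0.5, independence | .937 | 7.0 | 7.6–8.5 | 9.8 | 5.6 | 4.5 |
| Four-period, 0.8, independence | .908 | 8.7 | 8.2–9.1 | 11.7 | 6.4 | 5.0 |
| T1 covariate, 0, exchangeable | .905 | 8.7 | 8.4–9.1 | 11.2 | 5.6 | 3.7 |
| T1 covariate, 0.5, exchangeable | .926 | 8.1 | 8.0–9.1 | 10.6 | 4.8 | 3.5 |
| T1 covariate, 0.8, independence | .839 | 12.0 | 11.1–12.3 | 15.9 | 7.0 | 4.0 |

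A hand check: if the SE is too small by the factor r and the statistic behaves like t with 44 df, the true size is 2·P(t > 1.96·r). For r = .958, .905 and .839 this gives 6.7%, 8.3% and 10.7%, against 6.8%, 8.7% and 12.0% simulated.

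A separate simulation at the same rate and ICC, with region terms, gave 6.8–8.7% (four-period) and 8.3–10.7% (T1 covariate) for the plain sandwich. It gave 5.2–6.2% with KC + t and 3.0–4.9% with MD + t.

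**3. Cost in power at ICC .08** (equal sites, 1,004 replicates; plain z / KC + t / MD + t, in %).

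| Model, share of site variance common to periods | Primary (pooled) | HIV/HCV PC v HIV PC |
|---|---|---|
| T1 covariate, 0.8 | 99.9 / 99.7 / 99.5 | 80.0 / 74.1 / 68.2 |
| Four-period, 0.8 | 99.6 / 99.4 / 99.3 | 73.8 / 68.5 / 65.7 |
| T1 covariate, 0.5 | 97.8 / 96.8 / 94.6 | 61.0 / 53.8 / 48.3 |

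In the first row the secondary contrast loses 80.0 − 74.1 = 5.9 points (KC) or 80.0 − 68.2 = 11.8 points (MD). The other rows lose 5.3–8.1 and 7.2–12.7 points.

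**The case against.** The best defence is that the article says only that a sandwich estimator will be used. Kauermann-Carroll and Mancl-DeRouen variances are themselves sandwich estimators, so the text is compatible with a corrected analysis. The choice of variant and degrees of freedom is often left to an analysis plan, and none is shown. This stands in part. A reader might infer that the trial will use an uncorrected variance with a normal reference, but the article says neither. What remains is that the article does not leave the variance method open: it names one whose ordinary form is biased at this number of clusters, and adds nothing to control that.

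A reader might also infer a flat 10% error rate. The text does not support that. The upper figures need the T1-covariate reading, very unequal sites, or demographics entered as site-level covariates. Three such covariates plus three region terms gave 8.9–10.6% in a T1-adjusted simulation. Eligibility criteria describes testing counts supplied within gender and race/ethnicity categories, which points to demographics entering below site level. The four-period model is also the one the article literally describes.

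Nor can the inflation be called an excess over a stated rate, since no level is given. It is also not certain that each primary test rests on 34 sites: the primary contrast can be read as both PC arms against control, using all 51.

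**Conclusion.** The point holds conditionally. If no small-sample correction is applied, standard errors would be roughly 4–10% too small (up to 17% at a site-size CV of 0.8). The primary T3 contrast would run at about 7–9% under the four-period model, and at about 8–11% if T3 is modelled with T1 as a covariate or sites are very unequal. The one scenario that combined both reached 12.0%, and 2-df tests run higher throughout. Direction and rough size held in every scenario tried. The exact figure depends on inputs that the article does not give: test level, site-size variation, between-period correlation, covariate levels and working correlation.

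The primary power claim is not threatened. The 80% for the secondary contrast is: at ICC .08 it was reached only with strong baseline adjustment and the plain sandwich, whose true size for that contrast at ICC .06 was about 9%. This is a correction to settle before analysis, not a defect that undermines the design.

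**What to change.** State that all GEE contrasts, primary, secondary and tertiary, use a small-sample bias-corrected sandwich variance with a t or F reference on the number of sites minus the number of site-level parameters. With an intercept, two arm terms and three region terms this is 51 − 6 = 45; with T1 as a site-level covariate it is 44. If the analysis plan already says this, confirming it is enough.

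Choose between Kauermann-Carroll and Mancl-DeRouen in advance, by simulation under the planned model and plausible site sizes. With t, the former ran at 4.8–7.0% and the latter at 3.5–5.2% for the pooled contrast, so the first can remain slightly liberal and the second slightly conservative.

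The work is one sentence, a software option and a short simulation. Trial Status reports that data are still being collected, so this can be fixed before analysis. Primary power stays at about 95% or more. The secondary contrast loses about 6–12 points at ICC .08, partly because the uncorrected figure benefits from an inflated error rate. Its stated 80% should be recomputed and restated under the corrected test.

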## Cost Analysis

The quaternary outcome includes determining health outcomes, associated costs and evaluating the cost-effectiveness of the interventions. We will test the hypothesis that the incremental cost-effectiveness ratio (ICER) for the HIV PC intervention will be below a commonly-cited US willingness-to-pay threshold (<$100,000/quality adjusted life years (QALY)) and therefore more economically attractive than the control condition. Our other hypothesis is that the ICER for the HIV/HCV PC intervention will be more economically attractive than the HIV PC intervention. The study will follow a proven model of effective collaboration among the intervention team and computer simulation modelers to evaluate the health outcomes, health care utilization, and cost-effectiveness of the PC interventions (11). Established micro-costing techniques will be used to identify the costs of delivering the PC interventions, including personnel and non-personnel costs incurred centrally to deliver the intervention and incurred at the OTPs to participate in the intervention and conduct follow-up activities (excluding time required for research activities).

The micro-costing results and data on the characteristics of clients at each of the OTPs will be used as inputs to analyses conducted using the HEP-CE microsimulation model of HIV and HCV infections.(33, 34) These analyses will evaluate the incremental health outcomes, healthcare utilization, and cost-effectiveness of the PC interventions, considering the lifetime benefits and costs of linking to treatment clients newly identified as HIV-infected and as HCV- infected. The HEP-CE model will be used to conduct sensitivity analyses that consider a range of assumptions about key model parameters such as prevalence of undiagnosed HIV and HCV infection, effectiveness of linkage to care, likelihood of treatment initiation once linked, and likelihood of screening and linkage in the absence of the intervention. Separately, micro-costing data will be used to explore the budgetary requirements to scale up the PC interventions nationally, including the budget implications for participating OTPs. Sensitivity analyses will consider different scenarios for the sustainability of the interventions depending on level of success at institutionalizing testing practices.

## Qualitative Coding and Data Analysis

The development and application of a multi-level coding scheme is an integral component of the data analysis process. At the highest level of the coding hierarchy, are the primary analytic foci, coded as headings. Specific dimensions of the headings are assigned core codes, while dimensions of the core codes are assigned sub codes. We will use ATLAS.ti, a software program for qualitative analysis, to facilitate the analysis. Seven steps will be used to develop the coding scheme: 1) Identify the principal issues discussed by participants; 2) Construct definitions of the primary analytic themes; 3) Develop and apply core codes (themes) and sub codes (sub-themes) to the initial set of interviews; 4) Develop a provisional coding scheme; 5) Test the coding scheme by applying it to a subsample (n=15) of interviews 6) refine the provisional coding scheme; 7) Have two research team members independently apply the coding scheme to a new subsample (n=15) of interviews; 8) Have them meet to reconcile differences in their application of the codes; 9) Refine the coding scheme as needed and finalize it; and 10) Apply the finalized coding scheme to the full data set. Inter-coder reliability will be assessed with kappa statistic.

After all transcripts have been coded, the study team will extract and examine the content of text linked to specific core codes and sub codes and identify ways in which certain themes are analytically related. Identified relationships among themes may lead to more refined data searches. Once patterns of relationships among themes and issues are established, the study team will try to identify participants’ accounts that support or refute these patterns. Identifying and accounting for cases that “deviate” from an interpretative pattern enables us to test and confirm the pattern’s validity and robustness. Finally, the study team will attempt to map themes onto the relevant domains of the CFIR framework to assess the framework’s adequacy in identifying all the important factors supporting or impeding the adoption of testing. If emergent in these analyses, it will be possible to identify pathways through which adoption (of lack of adoption) of testing evolves in the PC versus the control conditions.

## Discussion

Our PC interventions, if shown to be effective and cost-effective, could be used at multiple levels to provide ongoing support to OTPs in delivering HIV/HCV testing. This promising approach should be adaptable to address HIV testing in other settings, including pharmacies, dental care settings, and community centers. To our knowledge, this study is the first to test organizational approaches to increase HIV and HIV/HCV testing strategies in OTPs. If successful, SAMHSA, HRSA, the AIDS Education and Training Center, the Addiction Technology Transfer Centers and other community-based agencies at the national, state, and local levels could use our organizational support approaches to provide ongoing support to SUD treatment programs in delivering HIV and HCV testing. This proposal is also well-aligned with the new National Institutes of Health (NIH)-wide guidelines for priorities for HIV/AIDS grants. The first priority is to reduce the incidence of HIV/AIDS and one of the main goals is to develop, test, and implement strategies to improve HIV testing and entry into prevention services.

Despite evidence highlighting the effectiveness and economic value in on-site HIV testing in SUD treatment programs, current testing practices are inadequate. There is an overall need for expanded HIV testing among persons who use substances, particularly in underutilized settings where high-risk persons receive health services. The I Test project is one of the first comprehensive studies to develop and test a PC intervention to support the adoption and implementation of HIV and HIV testing in opioid treatment programs. It is also novel in that it employs a study design that account for the integration of HIV and HCV testing in treatment programs, with a focus on linkage to care (35). Additionally, the translation of findings from this study is central, and is supported by the cost analysis. In light of the Affordable Care Act (ACA) facilitating initiatives to increase the provision and sustainability of HIV testing, therein lies a pivotal opportunity for OTP treatment sites to increase their continuous implementation of HIV testing and timely linkage to care. With cost barriers being largely negated, organizational barriers remain the predominant limiting factor in OTP sites’ uptake of testing; as such, our study is among the first to systematically test implementation strategies at the organizational level to promote the delivery of HIV testing in OTPs. By introducing a PC approach shown to be effective in primary care settings into OTP sites, our study aims to help sites navigate their reimbursement systems and mitigate staff-related barriers with the ultimate goal of bolstering timely HIV testing and linkage to care for those most in need.

## Trial Status

The trial is in the data collection stage, with the recruitment and randomization process nearly completed. Recruitment began 6/14/2017 and is expected to continue until late 2023. The protocol version number is 7.0, with date of 4/7/2021.

## Figures and Tables

**Figure 1. F1:**
[figure not shown]
Flow diagram Flow diagram of the trial design: cluster randomized controlled trial (RCT). The diagram illustrates the progression of sites through the different points of the study

**Table 1. T1:** Stage Theory of Organizational Change*

Concept		Definition	Application
1. Define problem (Awareness Stage)	1. Sense unsatisfied demands on a system 2. Search for possible responses	Problems recognized and analyzed; solutions sought and evaluated	Involve management and other personnel in awarenessraising activities
	3. Evaluate alternatives		
	4. Decide to adopt course of action		
2. Initiate Action (Adoption Stage)	5. Initiate action within system	Policy or directive formulated; resources for beginning change allocated	Provide process consultation to inform decision makers and implementers about what is involved in adoption
3. Implementation Stage	6. Implement the change	Innovation implemented; reactions occur and role changes occur	Provide training, technical, and problem-solving assistance
4. Institutionalizati on Stage	7. Institutionalize the change	Policy or program becomes entrenched in organization; new goals and values internalized	Identify high-level Champion (someone with decision making power or influence, beyond the implementation Champion), work to overcome obstacles to institutionalization, and create structures for integration

* Excepted from Glanz et al., 2008

**Table 2. T2:** Duration of Study and Assessment/Activities Schedule Once a given site enrolls in the study, its duration of participation is approximately 24 months broken into four distinct six-month-long intervals as visually depicted in the section 3.0 study flow diagram. Because the date on which a site is randomized to one of the three study conditions is considered to be Time = “0”, the timeline for a given site is depicted as running from month −6 to month 18 and the various assessments/activities occur within this timeline as follows:

Assessment	T1 (months −6 to −1)	T2 (months 1 to 6)	T3 (months 7 to 12)	T4 (months 13 to 18)
Aggregate (de-identified) Client Data Summary	X	X	X	X
Site Administrator Survey	X		X	
Clinician Survey	X		X	
State Administrator Survey	X		X	
Qualitative Interview -- Site Administrator/ Leader	X		X	
^1^Qualitative Interview -- Champion or Point Person	X		X	
^2^Brief Demographic Questionnaire		X		
^2^Readiness for Change Questionnaire		X		
^2^Practice Coaching Intervention Acceptability Questionnaire		X		
^3^Practice Coach Interaction Form		X		
^3^Quarterly Peer-to-Peer Evaluation		X		
^2^Cost Survey		X		
^2^Cost Interview (as needed)		X		

1 The baseline Qualitative Interview for the Champion (or point person receiving the information control materials) will be conducted immediately post-randomization so intervention sites have time to identify who will be the Champion.

2 Practice Coaches and Site personnel within sites assigned to an intervention condition will complete these assessments.

3 Practice Coaches will complete these activities/assessments throughout the intervention period to help inform cost analyses and (if one or both interventions are successful) the development of a refined manual to be used for “real world” PC implementation.

The intervention/control period is approximately 29 weeks or 6 months in duration. Interventionists (Practice Coaches) will engage OTPs over over the 6-month intervention to guide them through the process of improving the provision and sustained implementation of HIV or HIV/HCV testing services and linkage to care. Approximately 16 sessions (including an on-site visit) will occur during the intervention; the number of sessions will be greater in the first intervention phase and taper toward the last phase.

**Table 3. T3:** Protocol Specific Measures

Questions and Variables	Site Administrator Survey	Clinician Survey	State Administrator Survey	Qualitative Interviews

REIMBURSEMENT				
A. By Type of Source				
B. By Type of Service				
STAFFING				
CLIENT CHARACTERISTICS				
A. Percent with HIV or Risk Factors for HIV				
B. Percent with HCV or Risk Factors for HCV				
C. Percent with STIs or Risk Factors for STIs				
KNOWLEDGE				
A. Risk Behaviors				
B. Screening Methods				
C. Diagnostic Methods				
D. Treatments/Monitoring				
OPINIONS				
A. Regarding HIV/AIDS				
B. Regarding HCV				
C. Regarding STIs				
Questions and Variables	SURVEY A: Treatment Program Administrators	SURVEY B: Treatment Program Clinician	SURVEY C: State Administrators	Qualitative Interviews

PRACTICES/POLICIES				
A. Educational Programs				
B. Counseling				
C. Risk Assessments				
D. Screening/Diagnostic Tests				
E. Medical Hx/Physical Exam				
F. Treatments/Monitoring				
BARRIERS AND FACILITATORS TO IMPLEMENTING HIV AND HCV TESTING				

**Table T4:** Completed SPIRIT checklist

		Reporting Item	Page and Line Number	Reason if not applicable
